#### Inclusion and exclusion

Inclusion criteria involved not working (unemployed, on sick leave, or on social benefits), undergoing treatment for moderate to severe mental illness, having an expressed desire to work, and sufficient Norwegian reading and writing skills to be able to fill out the questionnaires.

#### Randomization

Upon receiving new eligible participants, trained and competent personnel at the IPS centers will perform an introductory interview with the participant, informing about the study, and asking the individual to fill out an informed consent form in order to be included in the study and receive an ID-number. When the participant has filled out the baseline-questionnaires, the person conducting the introductory interview contacts the research technician at Uni Research Health by email, stating the participants ID-number, gender, and year of birth. Using computer-generated randomization lists, the participant will be allocated to one of the two groups. A 2:1 randomization ratio will be applied the first months of recruitment to ensure that the IPS centers can run according to capacity. The randomization procedure will however strictly adhere to the formal requirements of adequate randomization at all times.

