#### Participants and recruitment

Eligible participants are patients currently undergoing treatment for moderate to severe mental illness, who are currently out of the labor market but have an expressed desire to work. They could be either unemployed, on sick leave benefits, or on other social benefits at the time of inclusion. Participants will primarily be recruited from the various District Psychiatric Centers (DPS), which are placed in secondary care, but could also be recruited from stepped-care initiatives located in primary care. All participants are or will be connected to a treatment-team linked to a job specialist (caseworker trained in IPS). We aim to recruit 200–250 participants in each group, with a total sample size of 400–500.

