#### Sample size calculation

Our estimates of sample size are based on international input-data from previous IPS-studies. As a general comparison, the typical sample size in the previous IPS studies range from 41 to 312 participants [33]. The studies from countries most similar to the Norwegian context include Australia (n = 41), England (n = 188), the Netherlands (n = 151), and Sweden (n = 120) [32,33]. For the non-US studies, the mean competitive employment rate was 50% for IPS and 20% for controls [33]. The study showing the lowest effect of IPS to this date came from England, with competitive employment rates of 22% for IPS and 11% for controls [48].

If we use 50% and 20% as possible rates, we will need 39 participants in each group in order to demonstrate a statistically significant difference (with a 5% significance level and power of 80%), and in a potential scenario with rates of 22% and 11%, we will need 178 participants in each group (Figure 1).

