#### Statistical analyses

The analyses will follow the “intention to treat” principle. We will apply administrative register data from NAV and SSB in order to evaluate the primary outcome of the project; labor market participation in ordinary paid employment and educational activity. Beyond giving consent at inclusion, this part of the effect evaluation is not dependent upon participants’ willingness to respond to surveys, as register data on employment, education and use of social security benefits will be complete for all participants. Consequently, common problems related to self-report such as recall bias, justification bias, and attrition will be avoided for our primary outcomes. Randomization helps to assure that there are no systematic differences between the IPS intervention and control intervention groups at baseline, in terms of both observable and unobservable characteristics. The design allows for a comparison of proportions employed in each group over time before and after inclusion, including a test of whether differences are statistically significant. Additionally, we will perform regression analysis using logistic regression models in order to a) control for any remaining variation in observable characteristics between groups, b) investigate which factors, other than IPS intervention, have an impact on labor market participation, and c) analyze heterogeneity in the response to IPS. Groups will be compared on secondary outcome measures using survey data at baseline, and after 6 and 12 months.

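### The allocation ratio changes during recruitment, but the planned comparison of proportions is not conditioned on allocation phase

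*Protocol article*

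**What the plan says.** All references are to the protocol article.

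- **Randomization:** "A 2:1 randomization ratio will be applied the first months of recruitment to ensure that the IPS centers can run according to capacity". The section promises formally sound randomization throughout. It does not say which arm the 2:1 favours, what ratio follows, when the switch occurs, or whether it occurs at all centers together.
- **Participants and recruitment:** "We aim to recruit 200–250 participants in each group, with a total sample size of 400–500".
- **Sample size calculation:** equal groups are used, for example "in a potential scenario with rates of 22% and 11%, we will need 178 participants in each group".
- **Statistical analyses:** "The design allows for a comparison of proportions employed in each group over time before and after inclusion", with a significance test. The supporting argument is that "Randomization helps to assure that there are no systematic differences between the IPS intervention and control intervention groups at baseline", for measured and unmeasured characteristics alike. Logistic regression is added, among other purposes to "control for any remaining variation in observable characteristics between groups". Allocation phase, recruitment period and center are not named as terms.

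**The concern.** Valid randomization within each phase does not make the pooled arms comparable when the allocation probability differs between phases. The arm favoured early on contains proportionally more early recruits. The stated purpose, keeping the IPS centers at capacity, implies that this arm is IPS. Recruitment period, and any prognostic factor that moves with it, is then systematically related to arm.

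Drift is plausible in this trial. Participants may come from secondary or primary care, so the case-mix can shift, and the labor market can change over the recruitment period. At stake is the primary comparison: the pooled difference could be shifted in either direction. A larger sample would not remove the shift, because it depends on proportions and not on numbers.

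**Working it through.** **1. The plan's own figures.** Pooled-variance formula, two-sided 5%, 80% power, equal groups:

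n = [1.960·√(2p̄(1−p̄)) + 0.842·√(p₁(1−p₁) + p₂(1−p₂))]² / (p₁−p₂)²

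- 22% vs 11%: p̄ = 0.165, so n = (1.029 + 0.437)² / 0.0121 = 177.6, i.e. 178. This matches.
- 50% vs 20%: p̄ = 0.35, so n = (1.322 + 0.539)² / 0.09 = 38.5, i.e. 39. This matches.

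The sample size calculation is reproduced, and it assumes equal groups.

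**2. Inputs that are not in the document (assumptions).** f is the share of participants randomized at 2:1 in favour of IPS, taken as 0.2 to 0.5. The remainder are randomized 1:1. The early–late difference in underlying employment (the drift) is taken as 10 points, with 20 points as a more extreme case.

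**3. Arm sizes.** IPS = N(1/2 + f/6) and TAU = N(1/2 − f/6).

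**4. Share of early recruits in each arm.** IPS: (2f/3)/(1/2 + f/6). TAU: (f/3)/(1/2 − f/6). Bias of the pooled difference = (IPS share − TAU share) × drift.

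| f | early share IPS | early share TAU | difference | bias, 10-point drift | bias, 20-point drift |
|---|---|---|---|---|---|
| 0.2 | 25.0% | 14.3% | 10.7 points | 1.1 | 2.1 |
| 0.33 | 39.6% | 24.7% | 14.9 points | 1.5 | 3.0 |
| 0.5 | 57.1% | 40.0% | 17.1 points | 1.7 | 3.4 |

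The difference peaks near f = 0.5; at f = 0.75 it is back to 13.3 points. The pooled comparison therefore carries at most about 17% of whatever drift exists.

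**5. Type I error of the pooled test.** N = 450, no true effect, normal approximation. For f = 0.5 with 20% employed among early and 30% among late recruits:

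- Expected proportions: IPS 0.571×20 + 0.429×30 = 24.3%; TAU 0.4×20 + 0.6×30 = 26.0%. Bias −1.7 points.
- Overall proportion 25%, arms 262.5 and 187.5: SE = √(0.1875 × (1/262.5 + 1/187.5)) = 4.1 points.
- Shift = −1.71/4.14 = −0.41 SE, so two-sided rejection is 7.0%.

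The same steps give 5.7% (f = 0.2) and 6.5% (f = 0.33). With 20% vs 40% the figures are 7.6%, 10.2% and 12.3% for f = 0.2, 0.33 and 0.5. With no drift the bias is zero and the level stays at 5%.

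**6. Do the arms stay within 200–250?** TAU ≥ 200 needs f ≤ 6(1/2 − 200/N). IPS ≤ 250 needs f ≤ 6(250/N − 1/2). Both must hold.

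| N | largest f that keeps both arms in range |
|---|---|
| 400 | 0 |
| 425 | 0.18 |
| 450 | 0.33 |
| 475 | 0.16 |
| 500 | 0 |

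Examples (IPS/TAU): N = 400, f = 0.33: 222/178. N = 450, f = 0.33: 250/200. N = 500, f = 0.2: 267/233.

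**7. Power for 22% vs 11%** at f = 0, 0.33 and 0.5: N = 400: 84.5, 83.7, 82.9%. N = 450: 88.4, 87.8, 87.2%. N = 500: 91.4, 91.0, 90.5%. The largest loss is 84.5 − 82.9 = 1.6 points.

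**The case against.** The strongest case against is that this concerns which covariates enter a model, a detail that a condensed article may leave to an analysis plan that is not shown. Nothing in the text excludes a phase term, and recruitment date is an observable characteristic that the logistic regression could include. The Quantitative material section controls for the local labor market through county indicators. The Data collection section provides three years of register data before baseline, so imbalance in prior employment would be visible. Center start-up mainly affects how IPS is delivered. A change in IPS quality over time is variation in the treatment effect, not confounding, and does not by itself inflate type I error.

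Much of this stands, and it limits the point. It does not remove it. The article states a comparison of proportions and a balance argument, and that argument is not true of the pooled sample once the ratio changes. Neither the unnamed regression covariates nor county indicators condition on allocation phase.

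Three stronger readings are tempting and are not supported:

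- *The target of 200–250 per group cannot be met.* It can be met at intermediate totals if the 2:1 phase is short enough, as step 6 shows.
- *The type I error is no longer 5%.* This holds only if outcomes drift with recruitment period, and the document gives neither the drift nor f.
- *Center is confounded with arm.* That would require centers to switch on different dates, which the document does not say.

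**Conclusion.** The point holds as a modest bias risk in the primary comparison that can be removed almost free of charge. Balance by randomization applies within each allocation phase, and the stated comparison pools across phases. If 20–50% of participants are randomized at 2:1 and the rest at 1:1, the pooled difference carries about 11–17% of any early–late difference in employment. For an assumed 10-point drift that is 1.1–1.7 points, against a planning difference of 22 − 11 = 11 points, with a type I error of about 6–7%. The direction cannot be known in advance.

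On arm sizes, equal groups are not to be expected. At a total of exactly 400 or 500, any 2:1 phase followed by 1:1 puts one arm outside the stated range. The effect on power is minor. The later 1:1 ratio, the direction of the 2:1, f and the drift are inferred or assumed, and the size of the problem rests on them.

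**What to change.** 1. In Randomization, state which arm the 2:1 favours, the ratio that follows, the rule for switching, and whether the switch is common to all centers.
2. Record for each participant the ratio in force at randomization.
3. Make the primary comparison conditional on allocation phase: a Mantel-Haenszel risk difference stratified by phase, or a phase term in the logistic model with a standardized risk difference. Use phase by center only if switch dates differ by center. Fix this before outcome data are seen.
4. In Statistical analyses, limit the statement on baseline balance to within allocation phase.
5. In Participants and recruitment, say that equal groups are not expected and give the expected arm sizes for the planned length of the 2:1 phase, for example about 222/178 of 400 if one third are randomized at 2:1.

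The cost is one stored variable, one stratification term and a few sentences. The loss of precision from a phase term is negligible, and comparing within phase removes this source of bias.

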#### Statistical analyses

The analyses will follow the “intention to treat” principle. We will apply administrative register data from NAV and SSB in order to evaluate the primary outcome of the project; labor market participation in ordinary paid employment and educational activity. Beyond giving consent at inclusion, this part of the effect evaluation is not dependent upon participants’ willingness to respond to surveys, as register data on employment, education and use of social security benefits will be complete for all participants. Consequently, common problems related to self-report such as recall bias, justification bias, and attrition will be avoided for our primary outcomes. Randomization helps to assure that there are no systematic differences between the IPS intervention and control intervention groups at baseline, in terms of both observable and unobservable characteristics. The design allows for a comparison of proportions employed in each group over time before and after inclusion, including a test of whether differences are statistically significant. Additionally, we will perform regression analysis using logistic regression models in order to a) control for any remaining variation in observable characteristics between groups, b) investigate which factors, other than IPS intervention, have an impact on labor market participation, and c) analyze heterogeneity in the response to IPS. Groups will be compared on secondary outcome measures using survey data at baseline, and after 6 and 12 months.

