## Methods/design

### Aims and objectives

The main aim of the study is to evaluate the effect of IPS compared to high quality TAU offered to people with moderate to severe mental illness in six IPS centers located in different Norwegian counties. We aim to address the following questions:Is IPS more effective than high quality TAU in terms of increasing labor market participation?Is IPS more effective than TAU in terms of improving mental health status and quality of life?Are there specific Norwegian policy factors that will influence the effectiveness of IPS?What are the challenges of implementing and disseminating IPS in a Norwegian context?Is IPS cost-effective compared to TAU?

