### Data collection

Survey data will be collected from both groups at baseline, 6 and 12 month follow-up. Baseline questionnaires will be administered and collected at the IPS centers by the person conducting the recruitment interviews. Data will be collected using iPads with secure survey software (Qualtrics®), but paper questionnaires will also be available. Electronic data will be collected in offline mode, before being connected to the Internet at the IPS center and sent to a secure online database. Paper questionnaires will be temporarily stored at the IPS center and forwarded to Uni Research Health every three months. Follow-up questionnaires will be administered electronically to participants who provide their e-mail address at baseline, or on paper via regular mail if this is preferred.

Using data from the national social insurance register and the national employee-register in Norway allows for complete and objective data to be collected every month for every participant, with no loss to follow-up. Data will be collected retrospectively 3 years before baseline, and prospectively 4 years after baseline [47]. This information will be collected for each month of follow-up, to examine sensitivity of the primary 12-months results. Additionally, the long follow-up ensures comparison with a recent Swedish IPS study, where effectiveness was first seen at 18 months [32].

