#### Quantitative material

The process evaluation includes collecting quantitative data that can describe how the different elements of the intervention were implemented. This information will be important in order to identify possible methodological challenges at the individual IPS centers, as expressed by the measures in the above framework: Reach, dose delivered and received, and fidelity. To explore local barriers towards successful implementation, we will also measure employers’ attitudes to hiring people who are at risk of being excluded from work life, as well as review characteristics of the local labor market.**Questionnaire items at 6-month follow-up:** 6**–**8 items will be included in the questionnaire at 6 months, measuring dose received, satisfaction, perceived efficacy, and perceived barriers and facilitators. The items are constructed based on process evaluation theory and adapted to the conditions of the current intervention.**Other data sources:** To determine the dose given, data will be collected from the job specialists’ register for each participant. To determine reach, the job specialists’ register of people who declined or accepted participation will be used. Publicly available statistical data will be used to examine the representativeness of the reached group in relation to the target group at large, using the variables age and gender.**Fidelity measurements:** The IPS fidelity scale is an established measurement [53], and the ratings will be carried out by a partly independent team that is trained, certified, and experienced in making such measurements. The measurements will be performed regularly throughout the project period. The fidelity ratings will evaluate the competence and methodology in conducting the intervention, as well as provide information on the frequency of contact and interaction with the participants. The qualitative interviews included in the fidelity measurements will provide a greater understanding and description of how the criteria have been attained, or why they may not have been attained. Although the process evaluation largely focuses on the IPS intervention group, qualitative interviews will also be conducted with participants in the control intervention group to get an idea of what control measures the ordinary follow-up has consisted of.**Questionnaire for employers:** The quality of the relationship between employer and employee can play an important role for commitment to the work place, job performance, and job satisfaction [54,55]. In order to examine attitudes towards hiring employees with various physical or mental illnesses and/or other limitations, researchers in the project group have developed a questionnaire that will be distributed to employers. In addition to providing a general overview of attitudes towards groups at risk of discrimination, we may also examine if any changes in attitudes occur after hiring employees with various challenges.**Local labor market:** The local labor market is likely to vary between the centers’ catchment areas, and availability of work can influence on the outcomes. Characteristics of the local labor market will therefore be controlled for, mainly by using county indicators such as structure and size of trade and industry, travel distances, unemployment rate according to gender and age group, and unemployment rate to vacant positions ratio.

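### The employment comparison at 12 months has no named primary analysis, and register history, center and allocation phase have no stated place in it; one prespecified adjusted model would use data already held

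*Protocol article*

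**What the plan says.** The Statistical analyses section says that the design allows a "comparison of proportions employed in each group over time before and after inclusion, including a test of whether differences are statistically significant". It then adds logistic regression with three aims: to "control for any remaining variation in observable characteristics between groups", to study other determinants of participation, and to examine heterogeneity of response. It does not say which analysis is primary, and it lists no covariates.

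The Sample size calculation section gives two scenarios at a 5% significance level and 80% power: "If we use 50% and 20% as possible rates, we will need 39 participants in each group" and "in a potential scenario with rates of 22% and 11%, we will need 178 participants in each group". The target is 200 to 250 per group.

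Other parts of the protocol bear on the choice of model:

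- Data collection: "Data will be collected retrospectively 3 years before baseline, and prospectively 4 years after baseline". These are monthly records, described as complete for every participant.
- Aims and objectives: the trial runs "in six IPS centers located in different Norwegian counties".
- Randomization: a 2:1 ratio applies in the first months. The later ratio is not stated, and no stratification by center is mentioned.
- Quantitative material, under the process evaluation: "Characteristics of the local labor market will therefore be controlled for, mainly by using county indicators".

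**The concern.** There are two candidate estimates for the primary outcome, crude and adjusted, and no order between them. Describing adjustment as a correction for leftover differences leaves room to settle the covariates, and the result to lead with, after the data are seen. That wording also misses the main reason to adjust in a randomized trial, which is that prognostic baseline covariates add precision whether or not they happen to be imbalanced.

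The strongest candidate covariate is already collected for everyone. Employment and benefit history over the previous 36 months may well predict employment at 12 months, yet its only stated link to the analysis is the comparison before and after inclusion.

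The change of allocation ratio raises a question of validity as well. If participants recruited in the 2:1 period have different outcome rates from later ones, the two arms hold different shares of early recruits. A comparison that ignores phase then carries part of the period difference into the treatment effect.

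County indicators raise a smaller point. With six centers in different counties, indicators that are constant within a county carry at most 6 − 1 = 5 degrees of freedom between them.

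**Working it through.** **1. Reproducing the plan's figures.** The inputs are the rates, the 5% level (taken as two-sided) and 80% power from the Sample size calculation section. The formula is the two-proportion formula with pooled variance under the null, 1:1 allocation and no continuity correction:

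n = [1.960·√(2p̄(1−p̄)) + 0.842·√(p₁(1−p₁)+p₂(1−p₂))]² / (p₁−p₂)²

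- 22% vs 11%: p̄ = 0.165, so n = [1.960×0.5249 + 0.842×0.5191]² / 0.0121 = 177.6, rounded up to **178**.
- 50% vs 20%: n = 38.5, rounded up to **39**.

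Both match exactly. The sizing is therefore for an unadjusted comparison of two proportions.

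**2. Power with adjustment.** Let R² be the share of outcome variance explained by the covariates. The documents give no value, so a range is assumed. The approximation is effective n = n/(1−R²), entered in

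power = Φ[((p₁−p₂)√n − 1.960·√(2p̄(1−p̄))) / √(p₁(1−p₁)+p₂(1−p₂))]

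For 200 per group, 22% vs 11% and R² = 0: (0.11×14.142 − 1.0289)/0.5191 = 1.015, giving 84.5%.

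| Scenario | n per group | R² 0 | R² 5% | R² 10% | R² 20% |
|---|---|---|---|---|---|
| 22% vs 11% | 200 | 84.5% | 86.3% | 88.0% | 91.4% |
| 22% vs 11% | 250 | 91.4% | 92.7% | 93.9% | 96.1% |
| 36% vs 25% (assumed) | 200 | 66.7% | 69.0% | 71.3% | 76.3% |
| 36% vs 25% (assumed) | 250 | 76.3% | 78.4% | 80.6% | 84.9% |

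The second scenario keeps the 11-point difference at a higher control rate. The protocol expects control rates above those in the international studies but gives no figure.

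**3. Simulation check.** The formula in step 2 comes from linear models, so it was checked with logistic fits. The set-up was six centers, 400 participants, the first 25% allocated 2:1 and the rest 1:1, and 1,500 runs per setting. The model had center and history but no phase term, and no period difference was simulated.

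| Scenario | R² (approx.) | Crude test | Center + history |
|---|---|---|---|
| 22% vs 11% | 0 | 84.4% | 84.1% |
| 22% vs 11% | 0.03 | 83.6% | 84.0% |
| 22% vs 11% | 0.08 | 85.1% | 87.5% |
| 22% vs 11% | 0.16 | 85.0% | 90.1% |
| 36% vs 25% | 0 | 65.1% | 64.1% |
| 36% vs 25% | 0.12 | 66.9% | 70.9% |
| 36% vs 25% | 0.22 | 67.3% | 77.4% |

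The direction and rough size agree with step 2. Center alone moved power by about 1 point either way, so nearly all the gain comes from history. Where the covariates predict nothing, the loss was about 1 point at most.

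**4. Allocation phase.** Assume 1:1 after the 2:1 period, because the two group targets are equal. Let s be the share recruited at 2:1 and d the difference in outcome rate between periods, the same in both arms.

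Bias = d × { (2s/3)/[2s/3+(1−s)/2] − (s/3)/[s/3+(1−s)/2] }

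- s = 0.15: 0.1905 − 0.1053 = 0.0852. With d = 5 points the bias is 0.43 points.
- s = 0.50: 0.5714 − 0.4000 = 0.1714. With d = 15 points the bias is 2.57 points.

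Over s = 15–50% and d = 5–15 points the bias is about 0.4 to 2.6 percentage points, against the 11-point planning difference. Its sign follows the period with the higher rate. If the rates do not differ between periods, it is zero.

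**5. County indicators.** A six-level center term uses 5 degrees of freedom and reproduces every difference that is fixed between counties. A county indicator that is constant over time adds nothing beside it. Unemployment by gender and age group, and rates that move during recruitment, are not absorbed.

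**The case against.** The best defense is that an unadjusted comparison of randomized proportions is a recognized analysis and matches the sizing. The covariate list and the ranking of analyses are normal content for a statistical analysis plan, which is not shown. That stands: the missing list is not an error, and the point is an improvement to a stated method.

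Several stronger readings are tempting, but the text does not carry them:

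- A reader might infer that the crude, center-pooled test is the designated main analysis. The section does not rank the analyses and does not exclude center. The match with the sizing is only suggestive.
- A reader might infer that covariates will be chosen by observed imbalance. The regression is planned unconditionally, no selection rule is given, and it also serves two other aims.
- A reader might infer significance testing of baseline differences. The phrase about before and after inclusion can equally mean a comparison of trajectories.
- A reader might want every county indicator dropped. That would discard those that vary by gender, age or time.
- A reader might take a 20% control rate as the higher rate that the plan expects. The protocol gives 20% as the mean control rate of the non-US studies.

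The size of the gain is also open to challenge. R² is assumed, and everyone is out of work at inclusion, which may limit what history predicts. At 22% vs 11% the crude test already exceeds 80% power at 200 per group, and it reaches 91.4% at 250. Both objections are fair. They bear on how much is gained and leave the case for prespecifying the model intact.

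**Conclusion.** The point holds as a low-cost improvement. The protocol describes a crude comparison and an additional regression without ordering them, and it gives register history, center and allocation phase no stated role as covariates in the primary comparison.

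The precision gain is conditional. It is about 2 to 7 power points at 200 per group for 22% vs 11% if R² is 5% to 20%, and close to nothing if history does not predict the outcome. The phase term has a separate purpose: it protects against a bias that could reach about 2.6 points at the upper end of the assumptions in step 4.

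Nothing here shows that the sample size is wrong; 178 and 39 per group are correct for the test they assume.

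**What to change.** Name one primary analysis of the 12-month outcome: a logistic model with

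- arm;
- center (six levels);
- allocation phase (2:1 period or later, coded by center if the switch dates differ);
- a fixed summary of the 36 months before inclusion, for example months employed and benefit type;
- age and sex.

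State that these terms enter whatever the observed balance. Report the effect as a standardized risk difference with 95% CI, so that the estimand is a difference in proportions rather than a conditional odds ratio. Keep the crude difference as supportive. Do not add purely county-level, time-fixed indicators beside the center term; those that vary by gender, age or time may stay.

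The cost is wording in the analysis plan, settled before outcome data are examined. The register history is already being collected for every participant, and no extra participants are needed.
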